Participants in this arm will also be offered pharmacological support to aid smoking cessation (nicotine replacement therapy or bupropion either separately or ideally in combination). Pharmacotherapies will be provided for a minimum period of three months. Participants who opt to take bupropion will be referred to their medical doctor for assessing suitability of prescribing bupropion. Participants will be offered sustained-release bupropion, 150 mg/d for the first week and 300 mg/d thereafter. The pharmacological support will be provided for free within the trial. The participants will be scheduled for prescribed medication collection during their face-to-face sessions. In case of changes in mobility restrictions as complying to the local government guideline for managing the upcoming Covid-19 pandemic situation, all scheduled prescribed medication shall be dispatched or personally delivered to the participants’ residential address by post or by research assistants, respectively. Medications for one month will be handed over to them personally by the research staff. An excel sheet log will be maintained for the dispensation, consumption, replenishing and monitoring of Bupropion/Nicotine gums for all the participants who choose pharmacotherapy. The excel sheet log will be filled for medication related details by the research assistants delivering the 4S intervention to the participants and will be centrally managed by the trial manager. The trial manager and the research assistant will monitor the excel sheet log daily to verify if patients would be close to finishing their one-month’s stock of Bupropion/Nicotine gums and need replenishment of a fresh stock. Patient participants who are close to finishing their medications will be given a telephone call one week in advance and asked to visit the NIMHANS campus again to collect the smoking cessation medication for another month; in case, they cannot come to collect the medications, the medications will be personally delivered to the patients. The medications will be provided for a period of three months in total. If there is requirement of bupropion/nicotine gums beyond three months, they will be referred to the treating clinical unit. The patients will be reimbursed the travel costs and compensated for the time they spent in procuring the medication from NIMHANS. The patients will be educated about the correct dosage and method of use, side effects of bupropion/nicotine gums along with an information leaflet on the medications and will be provided contact details to report side effects and for advice. A referral to emergency services will be facilitated in case of a serious adverse event. The participants will be informed to keep the medications in their safe custody and out of reach of children. bupropion/nicotine gums are medications that are routinely prescribed for smoking cessation, including for persons with severe mental illness. Suicide risk assessment will be carried out during the sessions in the intervention arm. Consent to contact family members in case the patient is not reachable on telephone will be sought to mitigate any risks associated with overdose. In case of overdose, a referral to the nearest emergency services will be facilitated. The adherence to medications will be documented in the counsellor’s record book in each session.

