#### Secondary outcomes

1. Self-reported or family/carer reported continuous smoking abstinence for at least six months (only five instances of smoking allowed during the total six months) which is biochemically verified by CO concentration (CO concentration <7ppm) at six months follow-up.^45^ This will be assessed at the longest possible follow-up point for those participants where it might not be possible to have a six months follow-up.
2. Point abstinence, defined as a self-report or family/carer report of not smoking in the previous seven days, assessed at one, three and six months follow-up. This will be assessed at the longest possible follow-up point for those participants where it might not be possible to have a six months follow-up.
3. Cost of delivering the IMPACT 4S and the BA interventions.

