#### Smoking status (baseline, one, three and six months)

Self-reported or family/carer reported smoking status will be assessed using the smoking questions from the GATS survey.^48^ At six months, self-reported smoking status will be biochemically verified by a CO level of <7ppm for those reporting that they have quit smoking, as per the Russell Standard.^45^ When a participant self-reports abstinence with an elevated CO level of >7ppm, the biochemical verification will supersede the self-report and the participant will be defined as a smoker. The CO assessment for biochemical verification of smoking status cannot be done in case of remote recruitment of trial participants or remote delivery of the 4S intervention to the trial participants

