### Frequency and duration of follow-up

Following randomisation and baseline data collection, participants in each arm will be followed up at one, three and six months post-randomisation. At each follow-up visit, a trained researcher will administer a structured follow-up data collection form to the trial participant, obtaining information according to the follow-up schedule below (Table 1). The study flow diagram is given in Figure 1 below.

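### Falling back on the latest available visit contradicts the six-month continuous-abstinence outcome and blurs the six-month point-abstinence rate

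*Protocol*

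**What the plan says.** Protocol section 5.14 (Secondary outcomes), repeated in the Summary, defines two abstinence outcomes.

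- Item 1 is "continuous smoking abstinence for at least six months (only five instances of smoking allowed during the total six months"), and it is "biochemically verified by CO concentration (CO concentration <7ppm) at six months follow-up".
- Item 2 is a participant or carer report of "not smoking in the previous seven days, assessed at one, three and six months follow-up". Its definition contains no CO reading at any visit.

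Both items carry the same fallback for people without a six-month follow-up: "This will be assessed at the longest possible follow-up point for those participants where it might not be possible".

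Other sections bear on what that fallback does:

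- Section 5.16: "participants in each arm will be followed up at one, three and six months post-randomisation". The only scheduled follow-ups before six months are therefore at one and three months.
- Section 5.15 (Smoking status): "At six months, self-reported smoking status will be biochemically verified by a CO level of <7ppm" for those reporting that they have quit. It adds: "The CO assessment for biochemical verification of smoking status cannot be done in case of remote recruitment" or of remote delivery.
- Section 5.1: in Arm 2, "The medications will be provided for a period of three months in total". The Summary spreads the counselling over three to four months. Arm 1 has one contact of up to five minutes on the enrolment day.
- Section 5.18: the event rates from this study are to inform the sample size of the definitive trial.

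**The concern.** The fallback does different damage to each outcome.

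For item 1 it is a contradiction. A person last seen at three months cannot satisfy a six-month definition, and no verification is scheduled at that visit. Two analysts could code the same person differently: one as unable to qualify, the other as abstinent so far.

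For item 2 it mixes time points. Abstinence at one and three months is already reported in its own right, so the fallback adds no information. It does allow a result obtained while Arm 2 is on treatment, or just finishing it, to stand in for a six-month result, with no matching treatment in Arm 1.

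At stake is the planning value of the pilot. A rate that belongs to no single time point is a poor input to the sample size of the definitive trial.

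**Working it through.** **The plan's own figure.** 120 / (1 − 0.30) = 171.4, rounded up to 172. The enrolment target reproduces.

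**Share that could be affected, f.**
- Section 3 gives the trial 12 months. With six months of recruitment (Summary) and six months per participant, 6 + 6 = 12, so everyone can reach six months: f = 0 if there is no other loss.
- If the fallback also covers ordinary loss, planned attrition gives up to 0.30 × 172 ≈ 52 people: f up to about 30%. This assumes that all of them were seen earlier.
- The Summary gives nine months for recruitment plus follow-up. With uniform accrual, only those enrolled in the first 9 − 6 = 3 of 6 months can reach six months: 3/6 × 172 = 86, so f is about 50%.

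**Item 1, direction.** Lapses only accumulate, so anyone within the five-lapse limit at six months was also within it at three. CO can only remove claimed quitters. Read as abstinence to date, the fallback therefore cannot lower the rate in either arm. Read strictly, nobody substituted can qualify, and if they stay in the denominator the rate falls to (1 − f) times its value.

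Illustration with f = 30% and assumed six-month rates of 15% (4S) v 5% (brief advice), which need 188 per arm at 90% power:
- Earlier rates 25% v 6%: 0.7×15 + 0.3×25 = 18.0% v 0.7×5 + 0.3×6 = 5.3%, or 133 per arm.
- Earlier rates 20% v 10%: 16.5% v 6.5%, or 212 per arm.
- Strict reading: 0.7×15 = 10.5% v 0.7×5 = 3.5%.

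So even where each arm's rate can only rise, the planned sample size may move either way.

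**Item 2, direction.** The protocol gives no abstinence rates, so all rates here are assumptions. Blended rate = (1 − f) × six-month rate + f × earlier rate. Sample size is for two proportions, two-sided 5%, 90% power:

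n = [1.960√(2p̄(1−p̄)) + 1.282√(p₁(1−p₁)+p₂(1−p₂))]² / (p₁−p₂)²

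For 15% v 7%: p̄ = 0.11, so n = (0.867 + 0.562)² / 0.0064 ≈ 319.4, or 320 per arm.

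| Assumed earlier rates, 4S v brief advice | f | Blended rates | n per arm |
|---|---|---|---|
| 25% v 8% (relapse after treatment) | 30% | 18.0% v 7.3% | 201 |
| 25% v 8% | 50% | 20.0% v 7.5% | 158 |
| 20% v 12% (equal inflation) | 30% | 16.5% v 8.5% | 358 |
| 10% v 7% (late quitting) | 30% | 13.5% v 7.0% | 456 |

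If the true rates are 15% v 7%, trials of 201 and 158 per arm have power of about 73% and 62%. The table does not bound the effect: late quitting with f = 50% gives 0.5×15 + 0.5×10 = 12.5% v 7.0%, which by the same formula needs 610 per arm.

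**The case against.** The strongest reply is that the protocol nowhere says earlier results are pooled into one six-month rate. Item 2 is already set at three visits, the planned analysis is descriptive, and a statistical analysis plan may keep the visits apart. That is fair for item 2: pooling is the natural reading of the fallback, not a stated fact. It does not help item 1, whose two sentences conflict on the page.

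The fallback may also be meant only for people whose follow-up is cut short by the calendar. Section 5.18, which keeps 120 for analysis after attrition, points that way. In that case the 30% share does not apply, and the number affected turns on the nine- or 12-month window. The latest point could also be an unscheduled contact at four or five months, but the protocol schedules none.

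A reader might infer more than the documents support:

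- That item 2 is inflated, mainly in Arm 2. Seven-day abstinence can rise as well as fall. Section 5.1 has Arm 2 participants cut down gradually, choose their own quit date and try again, so an early visit can understate the six-month rate. A larger effect in Arm 2 is plausible from the unequal treatment, but depends on relapse and missingness by arm, which are not given.
- That the definitive trial would necessarily be too small. Equal inflation or late quitting makes it larger.
- That substitution removes verification from item 2. Its definition has none to remove; that defect belongs to item 1. Arm 2 has CO readings at face-to-face sessions, but as feedback, not as outcome verification.

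**Conclusion.** The fallback is wrong as written and should be fixed. For item 1 the contradiction is certain, and so is the direction if the fallback means abstinence to date: each arm's rate rises or stays the same. For item 2 the six-month value may be blurred by earlier visits that fall within or at the end of treatment in one arm only; the direction is open.

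Under assumed six-month rates of 15% v 7%, sizing the definitive trial on blended rates gives about 158 to 456 per arm in the tabulated scenarios, against 320. These figures rest on assumed rates and on a share affected that runs from none, through up to about 30%, to about half. The upper share needs the nine-month window and uniform accrual.

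These are secondary outcomes, described rather than tested, in a feasibility trial. The primary feasibility outcomes are untouched, so this is a correction to make and not a reason to question the trial.

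**What to change.** 1. Delete the fallback sentence from items 1 and 2 in section 5.14 and in the Summary.
2. Restrict the six-month outcomes to six-month assessments, with item 1 requiring CO verification.
3. Report point abstinence at one, three and six months separately by arm, with the denominator shown.
4. Leave participants whose follow-up is administratively cut short before six months out of the six-month rate. They still contribute to the visits they reached.
5. For those due at six months but not seen, show the rate both as complete case and with missing counted as not abstinent. Neither should stand alone: at 30% missing, the second turns 15% v 7% into 10.5% v 4.9%, which would need 475 per arm instead of 320.
6. List separately those seen remotely at six months without a CO reading, whom item 1 cannot classify.
7. Reconcile the nine-month window in the Summary with the 12 months in section 3, since this decides how many people are cut short.

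The cost is wording only, with no new data collection. The downside is a six-month rate that rests on fewer participants and so has a wider interval.

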### Blinding

Blinding the participants and clinicians from knowing who is receiving the IMPACT 4S intervention or BA is not feasible. Outcome data collection and data analysis will also not be fully blinded.

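### Six-month point abstinence rests on report alone, yet the smoking-status rule lets CO above 7 ppm overturn a report without saying for which outcome, and leaves exactly 7 ppm unassigned

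*Protocol*

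**What the plan says.** Protocol section 5.14, Secondary outcomes, lists two abstinence outcomes, and the Summary table repeats both.

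- Item 1, continuous abstinence over six months, is reported by the participant or a carer, "which is biochemically verified by CO concentration (CO concentration <7ppm) at six months follow-up".
- Item 2 reads "Point abstinence, defined as a self-report or family/carer report of not smoking in the previous seven days". It applies at all three follow-up visits and has no CO criterion.

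Section 5.15, Smoking status, then gives a rule for the six-month visit:

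- Verification: "At six months, self-reported smoking status will be biochemically verified by a CO level of <7ppm for those reporting that they have quit smoking".
- Override: the trigger is worded "When a participant self-reports abstinence with an elevated CO level of >7ppm". The stated consequence is that "the biochemical verification will supersede the self-report and the participant will be defined as a smoker".
- Exception: "The CO assessment for biochemical verification of smoking status cannot be done in case of remote recruitment of trial participants or remote delivery". The delivery meant here is that of the IMPACT 4S arm.

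The opening of section 5.15 allows data to be collected remotely at every time point. On blinding, section 5.12 says participants and clinicians cannot be blinded and adds: "Outcome data collection and data analysis will also not be fully blinded".

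**The concern.** The override sits under a general heading on smoking status and names no outcome. Two analysts following the protocol could report different six-month point abstinence rates from the same data, one by report and one after CO reclassification. The two cut-offs in that paragraph also fail to meet: below 7 ppm verifies, above 7 ppm overturns, and 7 ppm itself does neither.

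This matters for two reasons. First, the trial is open-label and contact is very unequal: up to 15 counselling sessions in the IMPACT 4S arm against one contact of up to five minutes in the brief advice arm. Over-reporting of abstinence could plausibly differ by arm. Second, section 5.18 wants the trial to yield event rates for sizing a definitive trial, and the research questions ask whether CO validation is feasible and acceptable. An abstinence rate with two possible meanings serves neither aim well.

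**Working it through.** **Stated figure.** The enrolment target in section 5.18 reproduces: 120 / (1 − 0.30) = 171.4, rounded up to 172. It does not depend on how point abstinence is defined.

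**The rules side by side.** Take a participant seen face-to-face at six months who reports no smoking in the last seven days.

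| CO (ppm) | Point abstinence, 5.14 item 2 | Smoking status rule, 5.15 | Result |
| --- | --- | --- | --- |
| 6 | abstinent | verified | agree |
| 7 | abstinent | neither verified nor overturned | gap |
| 8 | abstinent | smoker | conflict |

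For continuous abstinence a reading of 7 is already settled, because item 1 requires CO below 7 and 7 fails. The gap therefore matters for point abstinence, and only if the override is meant to apply there. With remote recruitment or delivery there is no reading and the override cannot operate. Nor does the rule say whether CO overrides a carer's report.

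**Possible size in this trial.** Let s be the reported rate and f the share of reporters whom CO would overturn. The rate becomes s(1 − f), and 60·s·f participants per arm change class, taking 120 / 2 = 60 measured per arm. The protocol gives neither s nor f, so both are assumed, and every reporter is taken to have a reading.

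- s = 10%, f = 10%: 60 × 0.10 × 0.10 = 0.6 per arm; the rate falls from 10% to 9%.
- s = 20%, f = 30%: 60 × 0.20 × 0.30 = 3.6 per arm; from 20% to 14%.
- s = 30%, f = 50%: 60 × 0.30 × 0.50 = 9 per arm; from 30% to 15%.

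**Possible size for a definitive trial.** All inputs are assumed: reported rates 20% and 8%, two-sided 5% level, 90% power, two-proportion formula with pooled variance under the null. With p̄ = (p₁ + p₂)/2,

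n per arm = [1.960·√(2p̄(1 − p̄)) + 1.282·√(p₁(1 − p₁) + p₂(1 − p₂))]² / (p₁ − p₂)².

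For 20% versus 8% this gives 174 per arm. Power of 174 per arm for the verified rates:

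| False reports, 4S / brief advice | Verified rates | Difference (points) | Power |
| --- | --- | --- | --- |
| 10% / 10% | 18.0% v 7.2% | 10.8 | 86% |
| 25% / 25% | 15.0% v 6.0% | 9.0 | 78% |
| 25% / 10% | 15.0% v 7.2% | 7.8 | 64% |

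In the last row 339 per arm would be needed for 90% power.

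**The case against.** The best defence is that the two outcomes are deliberately different. Item 1 is the CO-verified one. The override is also at six months, uses the same figure of 7 ppm and cites the same standard, so it may be read as serving item 1 only. Item 2 then keeps one definition across three visits and can be collected remotely. On that reading a CO of 7 troubles neither outcome, since item 1 fails it and item 2 ignores CO. This is a sensible reading, but the protocol does not state it; the override speaks of smoking status in general. What stands is that requiring CO for point abstinence is not the only way to reconcile the two sections.

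A reader might also infer that CO is taken from every self-reported quitter, so that a verified definition could simply replace the reported one. The protocol does not support that. It rules out CO with remote recruitment or remote delivery, so a bare replacement would leave reporters without a reading unclassified. Because the remote-delivery exception names the 4S intervention, which only one arm receives, missing readings could be uneven by arm. Counting them as smoking could then penalise that arm, while dropping them would change the denominators.

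It is fair, too, that the analysis is descriptive, the outcome is secondary, and nothing says the definitive trial would be sized on unverified point abstinence.

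**Conclusion.** The point holds as a conflict between two stated rules, limited to six-month participants who report abstinence and have a CO reading. Above 7 ppm, sections 5.14 and 5.15 classify the same person differently. At exactly 7 ppm, section 5.15 assigns no class. Nothing is wrong at one and three months, where no CO verification is planned.

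The effect falls on the abstinence rates carried forward for planning: 0.6 to 9 reclassified participants per arm over the assumed range. It does not touch the 172 target. A reader might take the 64% power figure as the likely consequence. The documents do not support that: it comes from one assumed pairing of unequal misreport, equal misreport gives 86% or 78%, and none of these inputs is in the protocol. The point deserves correction because the repair is nearly free, but it does not threaten the trial's primary feasibility aims.

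**What to change.** 1. In section 5.15, Smoking status, change the override from above 7 ppm to at or above 7 ppm, so that it meets the verification cut-off.
2. State whether the override applies to six-month point abstinence, and whether it applies to carer reports as well as self-reports.
3. At six months, report two versions by arm: report-only point abstinence, and CO-verified point abstinence (a report of no smoking in seven days together with CO below 7 ppm).
4. Beside them give the number of reporters without a CO reading by arm. Show the verified rate twice: with missing CO counted as smoking, and among those with a reading.
5. Keep report-only point abstinence at one and three months.

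The cost is a lower verified rate and one extra descriptive table. No new measurement is needed, because the six-month reading is already planned for self-reported quitters wherever it can be taken.

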### Baseline and follow-up data collection

Data will be measured and collected from participants and carers face-to-face or remotely at baseline, one, three and six months. Data will be either be entered in paper format or directly into an online survey tool (Qualtrics)^46^ using tablets.

#### Demographic data (baseline)

The information on age and gender collected at the participant eligibility screening stage will be verified by asking the participant. We will also collect data on education, occupation, marital status, and on the possession of a number of household items to determine socio-economic status following the demographics module of the STEPs WHO questionnaire.^47^

#### Psychiatric medication use (baseline, one, three and six months)

Details of psychiatric medication that the participant is taking will be taken at baseline, and verified at each follow-up visit, in-order to capture any changes.

#### Smoking status (baseline, one, three and six months)

Self-reported or family/carer reported smoking status will be assessed using the smoking questions from the GATS survey.^48^ At six months, self-reported smoking status will be biochemically verified by a CO level of <7ppm for those reporting that they have quit smoking, as per the Russell Standard.^45^ When a participant self-reports abstinence with an elevated CO level of >7ppm, the biochemical verification will supersede the self-report and the participant will be defined as a smoker. The CO assessment for biochemical verification of smoking status cannot be done in case of remote recruitment of trial participants or remote delivery of the 4S intervention to the trial participants

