**Summary**

| Title | IMPACT Smoking cessation support for people with severe mental illness in South Asia (IMPACT 4S): a protocol for a randomised controlled pilot and feasibility trial for a combined behavioural and pharmacological support intervention |
| --- | --- |
| Short Title | IMPACT 4S pilot and feasibility trial |
| Version | V 1.3 |
| Date | 22/03/2021 |
| ISRCTN | ISRCTN34399445 |
| Study design | Randomised controlled pilot and feasibility trial |
| Study duration | 36 months (twenty-four months adaptation, nine months recruitment + follow-up, three months data analysis and report writing) |
| Population | Adults with severe mental illness (i.e. schizophrenia, schizoaffective disorder, bipolar affective disorder, psychosis, severe depression with psychosis) |
| Setting | Mental health facilities in India and Pakistan |
| Treatment(s) | *Brief advice*: five minutes, face-to-face, one-to-one smoking cessation counselling session and an information leaflet.  *Combined behavioural and pharmacological support intervention (IMPACT 4S intervention)*: The intervention comprises of up to 15 one-to-one and/or remotely delivered smoking cessation counselling sessions, each lasting between 15-40 minutes and spread over three/four months, breath carbon monoxide monitoring and feedback, pharmacotherapy (bupropion and/or nicotine replacement therapy), and an information leaflet. Remote sessions can be delivered using a number of different options such as telephone or video platforms (e.g. What’s App, messenger, Zoom etc.). |
| Study aim | To adapt an evidence based, combined behavioural and pharmacological support intervention for smoking cessation among people with severe mental illness; and test the feasibility of delivering and evaluating it in India and Pakistan. |

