The behavioural support will include BCTs chosen from a BCT taxonomy from a European context as no similar taxonomy has yet been developed for smoking cessation in LMICs^40^ and will also include BCT previously used for smoking cessation India.^41^ The BCTs will include goal setting, problem solving, social support, information about health consequences and adding objects to the environment. Participants will be encouraged to: (1) reduce smoking to quit, (2) set their own quit dates and (3) make several attempts to quit if their initial attempt fails. The IMPACT 4S intervention has been designed for either face-to-face, remote, or a combination of both face-to-face and remote sessions, to allow adaptation to practical feasibility and participants’ preferences. Remote sessions can be delivered using a number of different options such as telephone or video platforms (e.g. What’s App, messenger, Zoom etc.). The IMPACT 4S Intervention comprises of up to 15 one-to-one counselling sessions, each lasting between 15-40 minutes duration. Each session will be delivered by trained psychology graduates in Pakistan and psychology graduates and social workers in India. Delivery will be facilitated through the use of an intervention manual/guide, a flipbook containing key messages on how to quit smoking, and participants’ resource material. In the case of face-to-face delivery, the manual or flipbook will help intervention delivery staff to deliver messages via photo images on the front of the slides and text on the back of slides and same messages will be reiterated in posters and leaflets. This type of intervention delivery involving face-to-face mode is familiar for health and social workers as well and counsellors in these settings and has been found feasible and acceptable in the TB & Tobacco trial being conducted in Bangladesh and Pakistan.^34^ In order to facilitate the remote delivery of the intervention: 1) an adapted remote intervention manual will be use to deliver the intervention in a way that is consistent with face-to-face sessions; and 2) participants will be supplied with a set of seven-colour coded information sheets in advance that will provide information for each session, including any relevant ‘tasks’ that the participant will be required to complete for each session (e.g. smoking diary, reviewing the checklist for quit day and noting down reasons for stopping.

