#### Physical body measurements (baseline, three and six months)

Physical body measurements will include height and weight which will be measured by trained personnel according to the WHO protocols.^57^ These will be used to determine the body mass index. Physical body measurements of the trial participants will not be measured if the recruitment and assessments are conducted remotely, or the intervention is done delivered remotely.

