## OTHER ETHICAL CONSIDERATIONS

The study will commence following a formal ethics review and approval from the University of York’s Health Sciences Research Governance Committee. Ethics applications will also be submitted to the National (Indian Council of Medical Research, National Bioethics Committee Pakistan) and where required, institutional (such as the Ethics Committee (Behavioural Sciences Division), NIMHANS, Bangalore, India) levels in all participating India and Pakistan.

This study is part of a programme of research in South Asia called IMPACT. Approvals will also be sought collectively for the IMPACT studies from each administrative site in each participating country prior to commencement of IMPACT’s research activities.

The study will adhere to the fundamental principles of human rights and dignity laid down in the Declaration of Helsinki. Every possible effort will be made to uphold the principles of autonomy, justice, beneficence and non-maleficence in the design and conduct of the study. Firstly, the eligibility criteria are broad and inclusive to ensure inclusion of groups that may benefit from the trial. There will be no monetary benefits for recruited trial participants. Individuals will provide an informed consent and will have the right to discontinue participation at any point in the study. During study visits and data collection, efforts to minimize inconvenience and burden to participants will be maximised including seeking prior appointments for home visits if these are necessary. Enrolled participants will always be assured of complete confidentiality of their data; participant names will not be used.

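### Six-month CO verification depends on how a participant was recruited or treated rather than on how the six-month assessment is held, so verified abstinence is under-ascertained in the IMPACT 4S arm

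*Protocol*

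**What the plan says.** Secondary outcome 1 (section 5.14) is continuous abstinence reported by the participant or carer, "which is biochemically verified by CO concentration (CO concentration <7ppm) at six months follow-up". It applies to both arms.

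Section 5.15 (Smoking status) asks for CO at six months only from those who report having quit, and lets an elevated reading override the self-report. It then adds: "The CO assessment for biochemical verification of smoking status cannot be done in case of remote recruitment of trial participants or remote delivery"; the delivery it names is "remote delivery of the 4S intervention to the trial participants".

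The arms differ in mode. The Summary defines brief advice as a "five minutes, face-to-face, one-to-one smoking cessation counselling session and an information leaflet". Section 5.1 describes IMPACT 4S as "designed for either face-to-face, remote, or a combination of both face-to-face and remote sessions, to allow adaptation to practical feasibility" and to what participants prefer. Section 5.15 asks about preferred mode in the 4S arm only, so allocation is known by then.

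The opening of section 5.15 allows data collection at every time point, in either arm, to be face-to-face or remote. For height and weight, the same section says: "Physical body measurements of the trial participants will not be measured if the recruitment and assessments are conducted remotely", and extends this to remote delivery of the intervention.

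**The concern.** Whether a breath sample can be taken at six months depends on whether someone meets the participant at six months. The Summary spreads the 4S sessions over three to four months, so they are over by then, and their mode does not settle the question. The rule nevertheless uses session mode, and it names only 4S sessions.

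Followed as written, the rule withholds readings from Arm 2 quitters who were counselled remotely and sets no matching condition for brief advice. Mode is fixed after randomisation, by circumstances and by choice, so the quitters who remain verifiable in Arm 2 are a selected group.

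Two uses of the data are exposed. Section 5.18 justifies the sample partly by the event rates it will supply for the definitive trial. Section 2.3 asks whether CO measurement is feasible and acceptable, and for some participants the protocol answers this before they are asked. Data completeness (primary outcome 8) is affected too, for this one item.

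**Working it through.** **Inputs from the protocol.** Section 5.18: 120 to be retained, 30% attrition, 172 enrolled. Section 5: 1:1 allocation. The enrolment figure reproduces: 120 / (1 − 0.30) = 171.4, rounded up to 172, and 172 × 0.70 = 120.4. That leaves about n = 60 retained per arm.

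**Assumed inputs.** The protocol gives neither of these, so a range is shown.
- p: the proportion of retained Arm 2 participants who report quitting and whom CO would confirm. 15% is used for illustration.
- d: the share of Arm 2 counted as remotely treated: 25%, 50% or 75%, taken to be the same in quitters and others.
- No remote recruitment and no other lost readings, to isolate the delivery condition.

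**Formulas.** Participants who report smoking are classified without CO, so only quitters can lose their classification.
- Quitters without a reading: n × p × d.
- Rate if unverified counts as smoking: p(1 − d).
- Rate if unverified counts as missing: p(1 − d) / (1 − pd).

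**Arm 2, true rate 15% (9 of 60):**

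| d | Quitters without a reading | Unverified = smoking | Unverified = missing |
| --- | --- | --- | --- |
| 25% | 2.25 | 6.75/60 = 11.3% | 6.75/57.75 = 11.7% |
| 50% | 4.5 | 4.5/60 = 7.5% | 4.5/55.5 = 8.1% |
| 75% | 6.75 | 2.25/60 = 3.8% | 2.25/53.25 = 4.2% |

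**Comparison between arms (unverified = smoking).** With equal true rates of 10%, brief advice shows 10% and Arm 2 shows 7.5%, 5.0% or 2.5%. With true rates of 5% (brief advice) and 15% (4S), the ratio of 3.0 shows as 3.0 × (1 − d) = 2.25, 1.5 or 0.75.

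**Remote recruitment.** If a share s is recruited remotely, the expected share is the same in both arms, because recruitment precedes allocation. With unverified counted as smoking, both rates are multiplied by (1 − s) and their ratio does not change. At s = 20% and d = 0, 5% and 15% show as 4% and 12%, a ratio still of 3.0.

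**The case against.** The strongest defence is that the sentence in section 5.15 is loose pandemic-era drafting: it records a practical limit and is not a deliberate exclusion. The height-and-weight paragraph supports this, since it mentions remote assessments. Even so, the CO sentence does not mention the assessment at all, and site staff following it would not seek a reading from a remotely treated quitter who attends in person at six months.

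Several stronger readings are tempting, and the protocol does not support them.
- A reader might infer that the measured number in Arm 2 falls from 60 to about 30 at a 50% remote share, leaving only those treated face-to-face. It does not: reported smokers need no CO, so about 55.5 of 60 remain classified in the example.
- A reader might count remote recruitment as a source of imbalance between arms. It costs readings but acts before allocation (sections 5.5 and 5.11).
- A reader might treat the height-and-weight rule as identical. It is only partly so, because it also refers to assessment mode.
- A reader might say a real treatment difference would be lost. Section 5.18 plans descriptive summaries, so no test is at risk, and seven-day point abstinence (secondary outcome 2) needs no CO and is collected in both arms.
- A reader might take "seeking prior appointments for home visits if these are necessary" in section 9 as provision for CO testing at home. It is a general remark about visits, and section 11 sets room and protective-equipment conditions for CO testing.

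Other points stand as limits. Mode follows practicability as well as choice. Remote follow-up is allowed in both arms, so brief advice may lose readings as well. Section 5.1 does not repeat that brief advice is face-to-face, and the protocol does not say how someone recruited remotely receives it on the enrolment day; but the exclusion names 4S delivery only. How to classify a reported quitter with no reading commonly belongs in the SAP, which is not at hand, so its absence from the protocol is not counted as an error.

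**Conclusion.** The point holds in limited form. The rule makes ascertainment of secondary outcome 1 depend on arm through a post-randomisation factor, and the direction is known: verified abstinence in Arm 2 is understated under either classification of unverified quitters. An SAP can decide how to classify missing readings, but it cannot recover readings that the protocol says will not be taken.

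The size cannot be fixed from the protocol. It gives no remote share and no expected abstinence rate, and does not say whether a mixed course counts as remote delivery. If only fully remote courses count and these are rare, the effect is small; at an assumed half it roughly halves the Arm 2 rate.

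This is a should-fix. The outcome is secondary and the analysis descriptive, so the damage is confined to the event rates carried into the definitive trial and to what the pilot can say about the feasibility of CO measurement.

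**What to change.** In section 5.15 (Smoking status):
1. Delete the link between CO verification and recruitment mode or 4S delivery mode.
2. State that every reported quitter in either arm is asked for a CO reading at the six-month assessment wherever face-to-face contact is possible under local restrictions, and that CO is not done only when that assessment is itself remote.
3. Apply one identical rule in both arms to reported quitters without a reading, stated here or in the SAP, and report the percentage of reported quitters verified by arm.

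In the height-and-weight paragraph, make measurement depend on the mode of the assessment only.

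The cost is mainly wording, plus some travel for reported quitters who would otherwise be followed up remotely. If 10% to 20% of all 172 reported quitting, that would be at most 17 to 34 people (172 × 0.10 = 17.2; 172 × 0.20 = 34.4), and fewer in practice because some will attend in person anyway. CO monitoring is already part of the intervention, section 10.2 already refers to face-to-face follow-up visits, and section 11 already sets infection-control steps for testing. Some readings will still be lost when restrictions force a remote assessment, but the rule will then be the same in both arms.
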